#### Power calculation

Based on the experience of the 24 hours audit of EDs in England,^79^ and assuming that we would be able to recruit 50% of eligible ED attendees, we anticipated that the four sites (two Scotland, two England) would result in 940 recruits per week. Recruiting over 3 weeks pre-implementation and post-implementation—giving a total sample size of 5640 for the baseline and any one subsequent wave—would mean that we would be highly powered (>80%) to detect an effect size of ±5% in the proportion of alcohol-related attendances from an estimated 30% with 95% significance. We have used a base rate of 30% informed by the 24 hours audit of EDs in England^79^ and assumed a 5% decrease would be of public health importance and may be expected based on current evidence.^79^ For subgroup analyses, we would have good power (>80%) to detect an effect size of 0.23 on the FAST score among those from the most deprived quintile (estimated to be 25% of attendances) and an effect size of 0.27 among those aged 18–24 years (estimated to be 15% of attendances).

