**Methods and analysis:**

Component 1 sampled an estimated 2800 interviewees at a baseline and each of two follow-ups from four Emergency Departments in Scotland and Northern England. Research nurses administered a standardised survey to assess alcohol consumption and the proportion of attendances that were alcohol-related.

Component 2 covered six Sexual Health Clinics with similar timings and country allocation. A self-completion survey gathered information on potential unintended effects of MUP on alcohol source and drug use.

Using a natural experiment design and repeated cross-sectional audit, difference between Scotland (intervention) and North England (control) will be tested for outcomes using regression adjusting for differences at baseline. Differential impacts by age, gender and socioeconomic position will be investigated.

Component 3 used focus groups with young people and heavy drinkers and interviews with stakeholders before and after MUP implementation. The focus groups will allow exploration of attitudes, experiences and behaviours and the potential mechanisms by which impacts arise. The interviews will help characterise the implementation process.

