#### Outcome measures

The primary outcome will be the proportion of attendances that are alcohol-related, using a composite measure which defined the attendance as alcohol-related if any one (or more) of the following was true:patient self-reports attendance is alcohol-related;patient reports alcohol consumption in past 24 hours >8 units in men, >6 units in women; orpatient not approached or interview terminated because too intoxicated with alcohol.

Secondary outcomes will be:the absolute number and proportion of alcohol-related attendances;alcohol misuse defined by the FAST score >3;mean FAST score by age, gender and deprivation;prevalence of binge drinking in the past week, andself-reported reason for attendance.

Outcomes will be compared between intervention and control areas, adjusted for baseline attendances.

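### The >80% power stated for the Emergency Department study does not hold for the planned baseline-adjusted Scotland–England contrast, where it is about 55% with one follow-up and 67% with both

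*Protocol article*

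**What the plan says.** The Component 1 section on power expects that "the four sites (two Scotland, two England) would result in 940 recruits per week". Three weeks of recruitment per wave are then counted twice, "giving a total sample size of 5640 for the baseline and any one subsequent wave". The section concludes that this "would mean that we would be highly powered (>80%) to detect an effect size of ±5% in the proportion of alcohol-related attendances", from an assumed base rate of 30% at the 5% significance level. The abstract's figure agrees with the per-wave count: "Component 1 sampled an estimated 2800 interviewees at a baseline and each of two follow-ups".

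For subgroups, the same section says "we would have good power (>80%) to detect an effect size of 0.23 on the FAST score among those from the most deprived quintile", taken as 25% of attendances. It makes the matching claim for an effect of 0.27 at ages 18–24, taken as 15%. It does not name the contrast to which any of these powers applies.

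The analysis is described in three places. The abstract says that the "difference between Scotland (intervention) and North England (control) will be tested for outcomes using regression adjusting for differences at baseline". The Component 1 outcome section says "Outcomes will be compared between intervention and control areas, adjusted for baseline attendances". The Component 1 statistical analysis section enters ED as a fixed effect and adjusts for baseline levels of alcohol-related attendance. The study design section describes a repeated cross-sectional audit.

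**The concern.** Each of the four EDs lies in one country, so ED fixed effects absorb any constant difference between Scotland and England. The policy effect is then identified only by Scotland's change since baseline minus England's change. Each wave interviews different people, so nobody has a baseline value of their own that could reduce the variance. The estimate carries the sampling error of four independent groups. The stated power looks like that of a comparison carrying the error of two.

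The Introduction calls this evidence a key input to the decision on whether the policy continues, and the power section treats a 5-point fall as important for public health. If the result is not significant and is read beside a claim of high power, it will look like evidence against an important effect. With one follow-up, the chance of missing that effect would be about 45%.

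**Working it through.** **Inputs from the article.** 940 recruits per week over four EDs; 3 weeks per wave; baseline plus one follow-up; base rate 30%; change of 5 points; 5% significance; FAST effects of 0.23 (25% of attendances) and 0.27 (15%).

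**Assumptions.** Equal recruitment in the two countries; two-sided test; the 5% read as percentage points; FAST effects in SD units; no ED-by-wave variation. When both follow-ups are used, the effect is taken as equal at each.

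**Cell size.** 940 × 3 × 2 = 5640, so 2820 per wave and 2820 / 2 = 1410 per country per wave. The subgroup cells are 0.25 × 1410 = 352.5 and 0.15 × 1410 = 211.5.

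**Formula.** Power = Φ(effect / SE − 1.96). The difference detectable at 80% power is 2.80 × SE.

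**Step 1: a two-group comparison, 1410 against 1410.**
- 30% v 25%: SE = √[(0.21 + 0.1875) / 1410] = 0.0168; power 85%.
- 30% v 35%: SE = √[(0.21 + 0.2275) / 1410] = 0.0176; power 81%.

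Both agree with the claim of more than 80% for ±5 points.

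**Step 2: the baseline-adjusted contrast, one follow-up.** Three cells are at 30% and one has changed.
- Fall to 25%: SE = √[(3 × 0.21 + 0.1875) / 1410] = 0.0241; 0.05 / 0.0241 = 2.08; power 54.6%. Detectable difference 2.80 × 0.0241 = 6.7 points.
- Rise to 35%: SE = √[(3 × 0.21 + 0.2275) / 1410] = 0.0247; power 52.7%. Detectable difference 6.9 points.

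**Step 3: the same contrast, both follow-ups.** Each country has 2820 after implementation.
- Fall to 25%: SE = √[0.42 / 1410 + 0.3975 / 2820] = 0.0209; power 66.5%. Detectable difference 5.9 points.
- Rise to 35%: power 65.1%.

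**Step 4: FAST subgroups.** With m per cell and SD 1, the SE is √(2/m) for two groups, √(4/m) for the adjusted contrast with one follow-up, and √(3/m) with both.

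| Subgroup | m | Effect | Two groups | Adjusted, one follow-up | Adjusted, both | Detectable, one / both |
|---|---|---|---|---|---|---|
| Most deprived quintile | 352.5 | 0.23 | 86% | 58% | 70% | 0.30 / 0.26 SD |
| Age 18–24 | 211.5 | 0.27 | 79% | 50% | 62% | 0.39 / 0.33 SD |

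**Step 5: can another reading restore 80% for 5 points?** These variants use one follow-up.
- A one-sided test gives 67% for a fall and 65% for a rise.
- The log-odds scale gives 57% and 51%.
- A 5-point fall from a base rate of 20% gives 67%, and from 40% gives 49%.
- A relative change of 5% (30% to 28.5%) gives about 14% even for two groups.
- Covariates would have to remove 45–48% of the outcome variance.
- About 2570–2690 records per cell would be needed, or 10,300–10,800 over two waves, against 1410 and 5640.

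None does so on the information in the article.

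**The case against.** The power section states an inequality and names no contrast. A reader might infer that the authors must have used the 1410 v 1410 formula, but the text does not show that: 2820 against 2820 also exceeds 80% (about 98–99%). What stands is that the claim is consistent with a two-group comparison and not with the planned one.

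The 55% belongs to one follow-up, and two were collected. The analysis section plans a test of time by intervention, which suggests a model using all waves, where the figure is 67%. That is fair, and both figures should be given. The 55% answers the power section's own sample size, which counts a single later wave, and 67% is still short of 80%.

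Some other criticisms are tempting but unsupported:
- The two-group power of 79% at ages 18–24 is no separate error. The effect detectable at 80% is 2.80 × √(2 / 211.5) = 0.272, which rounds to the printed 0.27.
- The article nowhere makes each follow-up a separate primary test at 5%, so no inflated error rate can be charged to it.
- Whether a contrast pooling both follow-ups should be primary is a design choice that the unseen analysis plan may settle. The article deliberately asks whether the effect differs between time points.

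The composite outcome also counts some intoxicated patients who were not interviewed, which enlarges the denominator. Reaching 80% would take at least 80% more records per cell, and two of the three criteria rest on what the patient reports.

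Finally, all data had been collected when the article was revised, so the sample size cannot change. That limits what can be done, but the stated power is still wrong for the planned contrast.

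**Conclusion.** The concern holds. For the contrast described in the abstract, the outcome section and the analysis section, the stated power of more than 80% is too high for the primary outcome and for both FAST subgroup claims. On the primary outcome the shortfall from 80% is about 25 percentage points with one follow-up and about 13 with both.

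The size rests on the assumptions listed in the working. The article does not state the country split, the sidedness of the test or the FAST unit. Unequal recruitment or ED-by-wave variation would lower power further.

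A reader might infer that the analysis itself is unsound. The documents do not support that: no estimate or standard error is invalidated. What is wrong is the stated sensitivity of the study, and hence the weight that a null result would carry.

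**What to change.** State in the power section which contrast is powered, and restate the figures for the baseline-adjusted Scotland–England contrast together with the assumptions used:
- Primary outcome, 5-point fall: about 55% with one follow-up, 67% with both; detectable differences about 6.7 and 5.9 points.
- FAST, most deprived quintile: detectable effect about 0.30 SD with one follow-up, 0.26 SD with both.
- FAST, age 18–24: about 0.39 SD and 0.33 SD.

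Say that a non-significant result will be interpreted against these figures and the interval estimate. The change is to text only and needs no new data. Its cost is that the stated power becomes less favourable.

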#### Statistical analysis

We will test for differences in the outcomes between the intervention and control groups using a regression model with ED included as a fixed effect, and with individuals nested within the ED of their attendance, before and after adjustment for relevant covariates including baseline levels of alcohol-related attendance, age, gender, deprivation quintile and disease diagnostic categories. We will also attempt to determine the nature of the effect more precisely in terms of whether there is a dose-response effect according to the time since MUP was implemented (through a test of the significance of an interaction between time and intervention). We will test for interactions of the intervention with defined important covariates (including baseline levels of alcohol-related attendance, age, gender, deprivation quintile and disease diagnostic categories) to investigate the possibility of differential intervention effects and will subsequently stratify the analyses if indicated.

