## Methods and analysis

### Component 1: audit of alcohol-related attendances at EDs

#### Study design

This component is designed to quantify changes in alcohol-related attendances at ED settings as a result of MUP. The FAST is used to identify alcohol misuse in the ED. The component focuses on answering research aim (RA)1, namely:What are the impacts of MUP for alcohol on alcohol-related harms and drinking patterns (using the FAST) for ED attendees and by subgroups of interest (age, sex and deprivation)?Does the effect of MUP vary dependent on the type of alcohol-related harm:Acute alcohol-related harms vs chronic alcohol-related harms?Broad diagnostic groups (based on coding systems used in EDs?
Does MUP affect alcohol consumption (on the basis of the FAST^72^ score and alcohol misuse over the reporting period among people attending EDs (FAST >3)?Does the MUP intervention effect size (assessed on a variety of measures including FAST) vary at the second and third time points?

Lower level outcomes are set out in the Data collection section. To answer RA1, a natural experiment design employing a repeated cross-sectional audit of all alcohol-related attendances at EDs in two Scottish hospitals and two North of England comparator hospitals at three time points was most appropriate to assess causality. A Randomised Controlled Trial was not feasible. The study methods and tools were based on previous studies used to quantify the national prevalence of alcohol-related attendances in EDs in England^79^ and informed by the experience of the Scottish ED Alcohol Audit, carried out across 15–20 hospitals throughout mainland Scotland between October 2005 and June 2007.^80^

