#### Statistical analysis

Similar analyses to the ED component will be undertaken based on regression models with site included as a fixed effect, and the proportion taking illicit psychoactive drugs as the dependent variable for the primary outcome. We will examine whether any displacement effects are sustained between six and 12 months post implementation. We will investigate interactions with defined important covariates (including age, gender, highest achieved education, problematic drinkers) to investigate the possibility of differential intervention harms.

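### The ED model as written does not name an estimable MUP effect: country and baseline level are aliased with the ED fixed effects, and the interaction that could carry the effect is assigned to dose-response.

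*Protocol article*

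**What the plan says.** The Component 1 study design is an "audit of all alcohol-related attendances at EDs in two Scottish hospitals and two North of England comparator hospitals at three time points": one wave before MUP and two after. The abstract defines the contrast: "difference between Scotland (intervention) and North England (control) will be tested for outcomes using regression adjusting for differences at baseline". The Component 1 outcome section adds: "Outcomes will be compared between intervention and control areas, adjusted for baseline attendances".

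The Component 1 statistical analysis section opens with the main comparison: "We will test for differences in the outcomes between the intervention and control groups". It describes the model for this comparison as follows: "using a regression model with ED included as a fixed effect, and with individuals nested within the ED of their attendance". On adjustment, it says that results will be obtained "before and after adjustment for relevant covariates including baseline levels of alcohol-related attendance, age, gender, deprivation quintile". Diagnostic category is also on that list. A possible dose-response by time since implementation is then examined as a further step, "through a test of the significance of an interaction between time and intervention". Baseline level of alcohol-related attendance appears again in the list of effect modifiers. The section names neither a wave main effect nor a Scotland x post-MUP coefficient.

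The Component 1 study design section separately asks whether the size of the MUP effect differs between the second and third time points.

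Component 2 (three clinics per country) is to be analysed similarly, using "regression models with site included as a fixed effect".

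**The concern.** A fixed effect for each ED uses up everything that is constant within an ED. Country is constant within an ED. So is any baseline rate, because different people are interviewed at each wave and nobody carries a baseline value of their own. The main comparison that the text describes therefore has no separate coefficient in the model that the text describes.

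The term that can carry a difference-in-differences is the one between time and intervention. The article gives it a different job, that of detecting dose-response. An analyst following the paragraph could end up with any of these:

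- a country term that cannot be estimated;
- the Scottish before-after change alone, with the English control unused;
- the intended controlled effect;
- an overall effect labelled as dose-response.

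The introduction describes this evidence as a key input to whether the policy continues, and the research questions section says that analysis is about to start. The primary coefficient should be unambiguous before results are seen.

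**Working it through.** **Inputs.** From the article: 4 EDs, 2 per country; 3 waves, at 0, 8 and about 12 months from baseline; 940 recruits per week over four sites; 3 weeks per wave; base rate 30%. Assumed: equal recruitment across EDs, and the SD of ED-by-wave proportions, for which the article gives no figure.

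**The plan's own figure.** 940 x 3 weeks x 2 waves = 5640, as stated in the power calculation. Per wave this is 2820, and with equal split 2820 / 4 = 705 per ED per wave.

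**Step 1: aliasing.** With EDs 1 and 2 in Scotland, Scotland = ED1 + ED2, and baseline level = b1·ED1 + b2·ED2 + b3·ED3 + b4·ED4. Both are linear combinations of the ED indicators. Numerical ranks over 4 EDs x 3 waves (intercept and three ED indicators always included):

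| Terms added to ED fixed effects | Columns | Rank |
|---|---|---|
| country | 5 | 4 |
| baseline level | 5 | 4 |
| country + baseline level | 6 | 4 |
| country + baseline level + waves | 8 | 6 |
| Scotland x post-MUP, no wave effect | 5 | 5 |
| waves + Scotland x post-MUP | 7 | 7 |
| waves + Scotland x post-MUP + baseline level | 8 | 7 |
| waves + Scotland x wave 2 + Scotland x wave 3 | 8 | 8 |

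The first four rows cannot be fitted as written. The fifth can, but with no wave effect the English EDs inform only their own means, so the coefficient is the uncontrolled Scottish change. The sixth is the difference-in-differences. The seventh shows that baseline level adds nothing to it.

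**Step 2: the dose-response label.** Suppose intervention is coded as country, and MUP lowers the proportion by a constant 5 points at both follow-ups. The Scotland-minus-England differences relative to baseline are 0, -5, -5 at months 0, 8, 12. The mean month is 6.67. Sxx = 208 - 400/3 = 74.67 and Sxy = -100 + 66.67 = -33.33, so the fitted slope is -33.33 / 74.67 = -0.45 points a month. A time x country test would read this as a trend, although the effect did not change between the two post-MUP waves.

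**Step 3: ED-by-wave variation.** ED fixed effects remove stable differences between EDs, and nesting individuals in ED adds nothing to that. Neither covers a change specific to one ED between waves. For two waves, with SD s of the ED-by-wave proportions and p = 0.30:

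- individual-level SE = sqrt(2 x 0.21/705) = 2.44 points;
- true SE = sqrt(2 x (s² + 0.21/705));
- type I error of a nominal 5% test = 2 x [1 - Φ(1.96 x individual-level SE / true SE)].

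| Assumed s (points) | True SE (points) | Type I error |
|---|---|---|
| 0 | 2.44 | 5% |
| 1 | 2.82 | 9% |
| 2 | 3.74 | 20% |
| 3 | 4.89 | 33% |

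Simulation with 20,000 data sets gave 5.0%, 9.4%, 20.4% and 33.3%.

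**Step 4: Component 2.** Six clinic effects plus country: 7 columns, rank 6. Clinic effects + two wave effects + Scotland x post-MUP: 9 columns, rank 9.

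**The case against.** The strongest reply is that the word intervention can mean exposure to the policy, not the country. The Component 1 research questions speak of a MUP intervention effect size, and the abstract and outcome section both show that a baseline-adjusted comparison is intended. Coded as Scotland and post-MUP, with wave effects, the model has full rank and the redundant baseline term drops out. Under that coding, an interaction with time across the two post-MUP waves is the very comparison that the research question asks for. This stands. A reader might infer that the study cannot estimate the MUP effect, and the documents do not support that. It does not settle the text, because the abstract equates intervention with Scotland, and no wave effect is named under either coding.

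Three further limits also stand.

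- Collinearity does not rule out baseline level as an effect modifier: adding its product with Scotland x post-MUP to the ED + wave model gives 8 columns, rank 8. It would, however, rest on only two Scottish EDs.
- A reader might infer that the p-values are known to be too small. The article gives no ED-by-wave SD and no variance estimator, and the latter may properly be left to an analysis plan. The inflation is conditional on the assumed SD and is nil at zero.
- A reader might infer that Component 2 shares every defect. Its covariate list has no baseline level, and it labels nothing dose-response; it asks whether effects are sustained.

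**Conclusion.** The point holds as a defect in how the primary coefficient is fixed. Read with the article's own definition of intervention, the country main effect and the baseline-level main effect are both inestimable beside ED fixed effects (6 columns, rank 4). Read as exposure but without the unnamed wave effect, the model runs but discards the control. The intended effect is estimable from the planned data (7 columns, rank 7), but the paragraph does not say that it is primary. The mislabelling of a constant effect as dose-response arises only if intervention is coded as country.

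The rank results need only the site allocation and the repeated cross-sectional design. The type I error range of about 5% to 33% is illustrative: it assumes 705 attendees per ED-wave and an SD of 0 to 3 points. For Component 2, what carries over is the aliasing of country with the site fixed effects and the lack of any allowance for site-by-wave variation.

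**What to change.** Rewrite the Component 1 analysis paragraph as follows.

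- **Primary model:** outcome = ED fixed effects + wave fixed effects + Scotland x post-MUP, plus the individual covariates. State that the Scotland x post-MUP coefficient is the MUP effect.
- **Baseline level:** remove it as a main-effect covariate, since the ED effects already absorb it. If it is kept as an effect modifier, say that it rests on two Scottish EDs.
- **Change over time:** fit Scotland x wave 2 and Scotland x wave 3, and test the second minus the first. This answers the research question on the two later time points.
- **Sensitivity:** report the change in each ED separately, and show how the interval and p-value alter over a stated range of ED-by-wave SDs.

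In Component 2, name Scotland x post-MUP with site and wave fixed effects as the primary coefficient, with the same sensitivity analysis for site-by-wave variation.

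The cost is one rewritten paragraph for each component. The sensitivity intervals will be wider than the individual-level ones. No new data are needed.

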#### Data collection

Baseline data collection took place in February 2018 prior to the implementation of MUP on 1 st May 2018. The second and third waves of data collection took place approximately 8 and 12 months post baseline and 5 and 9 months post implementation, with care taken to avoid the inclusion of specific events that are expected to be associated with increased or decreased alcohol consumption, for example local holidays were checked to avoid differences between groups. Each wave collected data over 3 weeks, and to maximise collection of both alcohol-related attendances and alcohol misuse, data collection occurred from 20:00 to 03:30 from Thursday to Sunday (ie, 30 hours per week during this time period) and 09:00 to 16:30 from Monday to Wednesday (ie, 22.5 hours per week during this time period).

During study data collection periods, patients were approached by a research nurse to seek permission to complete a short face-to-face interview. All eligible patients were approached, informed consent obtained and a face-to-face interview based on a previously used patient questionnaire was administered electronically using a tablet (iPad).^78^ An ED attendance database was maintained for all attendances during data collection periods to allow monitoring of patient recruitment.

The interview collected details on the following:basic demographic information (age; gender; ethnicity; marital, employment and housing status (including unstable housing status such as no fixed abode and hostel accommodation); postcode sector);attendance details (date and time, triage category, time and date of incident);how much alcohol was consumed in the past 24 hours;date, time and place of last drink;the largest number of drinks on any 1 day in the previous week;self-reported reason for attendance, such as assault, collapse etc;alcohol misuse in the past year (as assessed by the FAST)^72^ andwhether alcohol consumption changed over the previous 12 months.

In addition we asked whether interviewees thought their current ED attendance was related to their or someone else’s drinking, and how many times they had attended any ED in the previous 12 months.

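### Component 1 plans to test whether the MUP effect varies with baseline level of alcohol-related attendance; on the design described, that test is a comparison of hospitals and cannot be attributed to baseline level

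*Protocol article*

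**What the plan says.** All references are to Component 1 of the protocol article.

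- **Study design** fixes a "repeated cross-sectional audit of all alcohol-related attendances at EDs in two Scottish hospitals and two North of England comparator hospitals", at three time points.
- **Statistical analysis** specifies "a regression model with ED included as a fixed effect, and with individuals nested within the ED of their attendance". Baseline level of alcohol-related attendance appears twice in this section: once among the adjustment covariates, and again among the effect modifiers, where the plan is to test "interactions of the intervention with defined important covariates (including baseline levels of alcohol-related attendance" as well as age, gender, deprivation quintile and diagnostic category. The stated purpose is "to investigate the possibility of differential intervention effects and will subsequently stratify the analyses if indicated".
- **Outcome measures** adds: "Outcomes will be compared between intervention and control areas, adjusted for baseline attendances".
- **Data collection** lists one item on each interviewee's own attendance history: "how many times they had attended any ED in the previous 12 months".
- **Power calculation** expects that "the four sites (two Scotland, two England) would result in 940 recruits per week", with three weeks of recruitment per wave.

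**The concern.** Age, gender, deprivation and diagnosis vary between people within an ED, so interactions with them draw on many individuals in every hospital. Baseline attendance level is different. Different people attend at each wave, and a person interviewed after implementation has no pre-implementation value of the outcome. If the baseline level is a figure for the hospital, the test has two distinct values in Scotland and two in England.

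The regression would still return an estimate and a p-value. That p-value would draw its apparent precision from some hundreds of interviews per ED and wave, although the modifier takes only four values. Stratifying on the result would mean stratifying by hospital. The results feed a decision on whether the policy continues, so a finding labelled as effect modification by baseline level could be read as evidence on where the policy works best. The design cannot supply that evidence.

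**Working it through.** **1. Inputs.** 940 recruits per week over four sites and three weeks per wave (Power calculation): 940 × 3 = 2,820 per wave, and 2,820 × 2 = 5,640 for two waves, which reproduces the article's total. An equal split over sites (assumed; the article gives only the total) gives 2,820 / 4 = 705 per ED per wave. The base rate is 30% (Power calculation). The article gives no between-ED variation, so the SDs below are assumed.

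**2. The plan's own power figure.** With 1,410 per country in one wave and two-sided 5%, power is 84.5% for 30% against 25% and 80.9% for 30% against 35%. The stated figure of more than 80% is reproduced, but it concerns the main contrast and says nothing about this interaction.

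**3. At what level can the baseline be measured?** The design is repeated cross-sectional. The one individual history item counts visits to any ED, so it is not specific to alcohol. For later waves, 5 and 9 months after implementation, its 12-month recall window includes months when MUP was in force. It is neither alcohol-related nor a baseline. The article describes no baseline rate by stratum within ED. That leaves one value per ED.

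**4. Rank of the design matrix**, with an ED-level baseline:

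- ED fixed effects alone: rank 4. Adding the ED baseline level: still 4. As an adjustment term it is fully redundant.
- The change over time needs four parameters (post, post × Scotland, post × baseline, post × Scotland × baseline). There are four ED changes, so residual degrees of freedom between EDs = 4 − 4 = 0.
- Against a model with ED × post: rank 8, 8 and jointly 8 with two waves; 9, 9 and jointly 9 with three waves. The two models span the same space.

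The interaction is therefore the difference between the two Scottish changes divided by their baseline gap, minus the same quantity for the two English EDs. Catchment, triage, staffing or recruitment differences between the hospitals would fit it equally well.

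**5. Standard error.** For the difference in change between two EDs, the individual-level SE is √(4 × 0.30 × 0.70 / 705) = √(0.84 / 705) = 3.45 points. If each ED-by-wave rate also varies with SD s, the true variance is 3.45² + 4s², while the test still uses 3.45².

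False-positive rate = 2 × [1 − Φ(1.96 × 3.45 / √(3.45² + 4s²))]

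| assumed ED-by-wave SD s (points) | true SE (points) | false-positive rate |
|---|---|---|
| 0 | 3.45 | 5% |
| 1 | 3.99 | 9% |
| 2 | 5.28 | 20% |
| 3 | 6.92 | 33% |

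This is written for one pair of EDs. For the full interaction, with rates near 30% and fixed baseline gaps g₁ and g₂, both the true and the assumed variance are multiplied by (1/g₁² + 1/g₂²). The factor cancels in the ratio, so the rates are unchanged.

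**6. Cross-check by simulation** (20,000 runs per setting, 705 per ED per wave, no true modification by baseline). The full interaction was rejected in 4.7%, 7.1%, 13.7% and 22.1% of runs for an SD of each ED's *change* of 0, 1, 2 and 3 points. The SD of a change is √2 times the ED-by-wave SD, so 4s² becomes 2 × SD². The formula then gives 5.0%, 7.0%, 13.0% and 21.6%. The two calculations agree.

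**The case against.** The strongest objection is that the article never says that the baseline level is one number per ED. A baseline rate could be formed by stratum within each ED, for example by age and sex or by the night and day sampling windows, which would give more than four values. How a covariate is built is often left to a full protocol or SAP, neither of which is shown. This stands in part: the ED-level reading is inferred. But the article describes no such strata, and strata built from age, sex and deprivation would largely restate interactions already on the list.

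Second, the false-positive rates rest on assumed SDs, and the rate is nominal when ED-by-wave variation is zero. Unmodelled variation of this kind also affects the main Scotland–England contrast, so it is not a problem peculiar to this test. Both points stand. The aliasing is what is specific to this test, and it does not depend on any assumed SD.

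Third, the analysis is exploratory. The subgroups named in the research aims are age, sex and socioeconomic position, and the article announces no claim about baseline level. This also stands and limits the weight of the point. It does not make the test interpretable.

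A reader might go further and infer that all the planned interaction tests fail, or that the article plans to claim that MUP works better where baseline alcohol-related attendance is higher. The documents support neither: the other listed modifiers vary within EDs, and no such claim is planned.

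**Conclusion.** The point holds for one item in the list of effect modifiers. On the design described, the interaction of the intervention with baseline attendance level cannot be distinguished from a comparison of hospitals: four values, two per country, no residual degrees of freedom between EDs. No result from it, significant or not, can be attributed to baseline level.

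This conclusion rests on reading the baseline as an ED-level quantity, which is inferred from the repeated cross-sectional design and the listed data items. The inflated error rates of about 9%, 20% and 33% are illustrations for assumed SDs of 1, 2 and 3 points with equal ED sizes. They should not be read as estimates for this study.

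On the same reading, the baseline term in the adjustment list is redundant with the ED fixed effect. That is harmless to the estimate. The point does not affect the primary analysis or the interactions with age, gender, deprivation and diagnosis.

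**What to change.** In the Component 1 Statistical analysis section:

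- Remove baseline level of alcohol-related attendance from the list of covariates for interaction tests and stratification.
- Report the change in each of the four EDs descriptively, with confidence intervals, labelled as hospital heterogeneity.
- Drop the ED-level baseline term from the adjustment list, since the ED fixed effect already absorbs it.
- Keep the interactions with age, gender, deprivation quintile and diagnostic category.

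The change is one of wording. The article says that data collection is complete and analysis is about to begin, so the change should be recorded before results are seen. The only loss is one test that could not be interpreted.
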